### Co-existent treatment

A record of co-existent treatments, both pharmacological and non-pharmacological, will be recorded for every participant. Any treatment pertaining to smoking cessation should be discontinued at the start of the run-in week and will not be resumed until the participant completed the study or is withdrawn from the study due to treatment failure or adverse events. Equally, all participants will be advised not to attempt any smoking cessation 2 weeks before the run-in period.

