### Outcome measures

The primary outcome measures in our study will be 7-day point prevalent abstinence rate (PAR), continuous abstinence rate (CAR), end-expiratory carbon monoxide levels (CO), nicotine withdrawal symptoms according to the Minnesota Nicotine Withdrawal Scale (MNWS) and stress level according to the Stress Check List (SCL). PAR is defined as abstinence from tobacco smoking for the previous 7 days, whereas CAR is defined as abstinence since the target quit date. The time taken (T) to reach the quit date is also recorded. During the active intervention period (week 2 to week 7), the following will be assessed weekly: number of cigarettes smokes per day, CO, MNWS and SCL. At week 3, 5 and 7, CAR and PAR will be assessed. At week 13 and week 26, successful quitters will be assessed for CO, PAR, SCL and MNWS. At week 2 and week 8/one week after successful quitting, expectancy of treatment will be assessed in all participants with a modified 4-item Borkovec and Nau self-assessment credibility scale as adopted by Tough *et al. *[40] in acupuncture related studies.

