### Adverse events and withdrawal from studies

Part of the objectives of our pilot study is to assess the possible adverse effects due either to the auricular acupressure or, due to withdrawal and stress from smoking cessation. The nature and severity of the adverse effects will be recorded and assessed with the MNWS and SCL scores. At any time, participants may withdraw from the study if they develop severe nicotine withdrawal reactions or anxiety symptoms; if they have any adverse effects of pain, discomfort, inflammation or infection at the local sites of the plaster; if there is any inter-current illness that would, in the judgment of the investigators, affect outcome measures to a significant degree; and finally, as requested by the participants.

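### Symptoms and plaster-site effects are grounds for leaving the study rather than stopping treatment, so later primary-outcome scores and event outcomes can be lost selectively

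*Protocol article*

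**What the plan says.** Under Adverse events and withdrawal from studies, the article states that "participants may withdraw from the study if they develop severe nicotine withdrawal reactions or anxiety symptoms", or "if they have any adverse effects of pain, discomfort, inflammation or infection at the local sites of the plaster". The second ground has no severity threshold. Intercurrent illness and the participant's own request are listed as further, separate grounds. The same section makes it an objective to assess harms of the acupressure and harms "due to withdrawal and stress from smoking cessation", and uses the MNWS and SCL scores to assess them.

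Under Co-existent treatment, other cessation therapies have to stop when run-in begins. They stay off limits "until the participant completed the study or is withdrawn from the study due to treatment failure or adverse events".

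Under Outcome measures, MNWS, SCL, CO, PAR and CAR are all primary. For weeks 2 to 7, "the following will be assessed weekly: number of cigarettes smokes per day, CO, MNWS and SCL". Abstinence has its own schedule: "At week 3, 5 and 7, CAR and PAR will be assessed". Later, "At week 13 and week 26, successful quitters will be assessed for CO, PAR, SCL and MNWS".

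**The concern.** The text describes leaving the study where stopping or changing the treatment would do. Mild discomfort under a plaster qualifies, although taking the plaster off would deal with it and the weekly visits could go on. No step is described in which a participant stops treatment and keeps attending.

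The grounds are not neutral. Severe nicotine withdrawal and anxiety are close to what MNWS and SCL measure, treatment failure bears on abstinence, and local effects are central to the safety aim. Anyone who leaves on these grounds takes away the later scores and the outcome of the event, and does so because of their condition. The plaster-site route is closed to Arm 3, so in comparisons with that arm it is unequal by design.

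At stake are a possible understatement of harm in an arm that causes more of it, and an incomplete safety record in a pilot meant to show that the method is safe. The pilot is also meant to supply the effect size for later trials.

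**Working it through.** **No planned figure is at issue.** The sample of 60 (3 × 20) is a convenience sample with no power calculation behind it, so there is nothing to reproduce beyond that product.

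**Data lost per exit, from the article's schedule**
- MNWS, SCL and CO are due at weeks 2, 3, 4, 5, 6 and 7: 6 assessments. Exit just after the week 3 visit loses weeks 4 to 7: 4 of 6.
- PAR and CAR are due at weeks 3, 5 and 7: 3 assessments. The same exit loses weeks 5 and 7: 2 of 3.
- Weeks 13 and 26 apply only to successful quitters, so a non-quitter who leaves loses nothing there.
- One exit is 1/20 = 5% of an arm.
- The event that triggers exit and the scores up to that point are kept. What goes missing comes afterwards.

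**Illustration of bias (inputs assumed, not in the article)**
- Six equally correlated normal weekly scores, with correlation 0.5 or 0.7.
- One arm truly 0.50 SD higher.
- Severe means the top 5% or 10% of the other arm's distribution.
- A severe score in weeks 2 to 6 leads to exit with probability 0.25 or 0.50.
- The result is the week 7 difference.

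| Exit rule | Exits, higher v lower arm | Observed cases, SD | Regression on earlier recorded scores, SD |
|---|---|---|---|
| Recorded severe score, probability 0.25 | 12–22% v 5–11% | 0.40–0.44 | 0.50 |
| Recorded severe score, probability 0.50 | 20–36% v 9–19% | 0.34–0.40 | 0.50 |
| Severe score never recorded, either probability | same ranges | 0.32–0.43 | 0.41–0.48 |

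The Hodges-Lehmann estimate, which the article plans to report, gives nearly the same as the means under the recorded rule: 0.40–0.44 and 0.33–0.39. A simpler model, with one earlier score correlated 0.6 with the final one, shows the 0.50 SD difference as 0.37–0.48 SD in medians.

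**Set against precision.** The standard error of a 20 v 20 difference is √(2/20) = 0.32 SD. The largest observed-case shift is 0.50 − 0.32 = 0.18 SD. The sign never changes. With equal score distributions and the same exit rule in both arms, the shift is zero within simulation error.

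**What following everyone would give.** If participants who stop take other treatment that lowers their scores by an assumed amount, the week 7 difference is 0.50 − (lowering × gap in stopping). The gap runs from 0.12 − 0.05 = 0.07 to 0.36 − 0.19 = 0.17. A lowering of 0.5 SD gives roughly 0.415 to 0.465 SD; a lowering of 1 SD gives 0.33 to 0.43 SD.

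**The case against.** The first ground is worded as a permission: participants may leave, and nothing says they must or that a participant may not remove the plasters and keep attending. A condensed article can leave the mechanics of stopping and event follow-up to a full protocol, and missing-data handling to an analysis plan. Counting leavers as smoking, or giving symptom exits a worst rank, would limit the damage. These points stand as limits on size. They do not remove the point, because the article does state that the exit is from the study, and the Co-existent treatment section speaks more firmly of a participant who is withdrawn. An analysis plan governs how data are analysed and cannot restore scores or event outcomes that were never collected.

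A reader might also infer that the bar on resuming cessation treatment pushes participants in distress out of the study. The article does not support this as a strong incentive. The exclusion criteria remove anyone on existing cessation pharmacotherapy, and participants are advised against any cessation attempt in the 2 weeks before run-in, so few should have a treatment to resume. Read more broadly, as a bar on new treatment, it is a deliberate way to keep the arms free of co-treatment.

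Finally, continued follow-up may not recover the 0.50 SD contrast: with a 1 SD benefit from other treatment, the result is about what observed cases give. That is fair. But the retained comparison then covers everyone randomised, with the other treatment visible, and the event outcomes are known, which no model can supply.

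**Conclusion.** The point holds as an inexpensive improvement to conduct. As written, the plan allows, and in one place presupposes, study exit on grounds that overlap the primary outcomes and the safety aim, with one ground available in only two of the three arms. The certain part is the loss per exit: up to 4 of 6 weekly assessments and 2 of 3 abstinence assessments for an exit after week 3, plus the outcome of the event.

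The bias cannot be sized from the article. It depends on how many participants leave, whether the arms differ, and how the gaps are analysed, and none of these is given. A reader might infer that the results would be seriously distorted. The illustration does not support that: it assumes a real 0.50 SD harm and up to 36% exits, yet the direction is kept, the shift stays below one standard error, and a model using recorded scores removes it when exit depends only on those scores. The firmer reason to act is the safety record. Whether a local infection resolved, or how long severe withdrawal lasted, can be learned only by continuing to see the participant.

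**What to change.** Amend two sections.

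- In Adverse events and withdrawal from studies, make plaster-site effects, severe nicotine withdrawal and anxiety grounds for removing the plasters (Arms 1 and 2) or otherwise modifying treatment. Reserve study exit for participants who decline further follow-up. Their right to leave at any time is unchanged.
- In Co-existent treatment, treat adverse events and treatment failure in the same way, as reasons to stop or change treatment and not as reasons for withdrawal from the study.
- Take MNWS and SCL when treatment stops, continue the scheduled assessments to week 7 (and weeks 13 and 26 for successful quitters), and follow adverse events to resolution.
- Record any cessation treatment then used, and report stops by reason and arm.

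Counselling in Arm 3 need not stop; ending it would be an odd response to severe withdrawal. Whether the bar on other cessation treatment ends when the plasters come off is a clinical choice for the sponsor to state. The change works either way, provided that what is used is recorded.

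The cost is an amendment to two short sections and a few more attended visits that are already scheduled. Later scores may partly reflect other treatment and must be shown alongside it.

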### Sample size calculation and randomisation

A convenience sample size of a total of 60 participants will be recruited, with 20 participants per arm after randomisation. Compared to other pilot studies, this sample size is deemed sufficient and appropriate statistical methods will be adopted to accommodate for foreseeable limitations during final analysis (see section on statistical analysis). Randomisation and allocation of subjects will be performed according to the CONSORT standards in terms of randomisation type[37], randomisation generation[38], allocation concealment[39]. All participants will be informed that they will be randomly allocated to one of the three study arms using a computer generated sequence created by the SPSS 11.0 (IBM^© ^SPSS^© ^Statistics, NY, USA). The random allocation will only be disclosed on the date of treatment commencement. Apart from Arm 3 (passive controls with no acupressure), blinding will be ensured in participants of Arm 1 (true acupuncture points) and Arm 2 (sham points). In particular, participants receiving acupressure will be told that the actual points chosen may vary over time to eliminate guessing amongst them during the study. Efforts will also be made to avoid contacts between all participants.

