### Auricular acupressure

Auricular acupressure will be administered by research assistants and staff nurses who will attend a one-day training course. They will be naïve to the differences between the true and sham acupressure points, and will be advised not to discuss anything with the participants. Their competence and point accuracy will be assessed before the start of the study and periodically thereafter by the research team and two licenced practitioners in acupuncture.

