### Sham acupressure (Arm2)

As active controls, participants in Arm 2 will receive identical acupressure plasters bilaterally as in Arm 1 except that the 5 auricular points are randomly chosen with none belonging to the NADA points, or any other true acupressure points that have been described. If in doubt, the principal investigators will be consulted. As in Arm 1, participants in Arm 2 will also be instructed to exert firm digital pressure to every acupoint via the plastered seeds for five seconds whenever they feel the urge to smoke. Similarly, if the plasters detach at any time of the study, they need to be replaced without delay. Period of treatment will be six weeks (week 2 to week 7).

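### Withdrawal from the study is allowed for an intercurrent illness because the investigators expect it to affect the outcome, and that judgement is not stated to be blind to arm

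*Protocol article*

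**What the plan says.** Under the heading on adverse events and withdrawal, the protocol article lists four kinds of ground for leaving the study. It opens with "At any time, participants may withdraw from the study if they develop severe nicotine withdrawal reactions or anxiety symptoms", then gives local effects at the plaster sites, then an "inter-current illness that would, in the judgment of the investigators, affect outcome measures to a significant degree", "and finally, as requested by the participants". The third ground is the one at issue. Its criterion is the effect on the outcome measures, and the investigators apply it.

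The section on co-existent treatment shows that withdrawal need not be the participant's own act, since it speaks of someone who "is withdrawn from the study due to treatment failure or adverse events".

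On blinding, the section on sample size and randomisation says that "blinding will be ensured in participants of Arm 1 (true acupuncture points) and Arm 2 (sham points". Arm 3 is exempted. The section on auricular acupressure adds that the staff who place the plasters will be "naïve to the differences between the true and sham acupressure points". The sham section says of the choice of sham points: "If in doubt, the principal investigators will be consulted". The article does not state whether the investigators who would judge an illness are blind to arm.

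**The concern.** A participant's safety and consent are legitimate reasons to leave a trial, and both have their own place in the list. The illness ground is different: a person may go because the illness is expected to move the result. Loss after randomisation is then related to outcome by construction. If the judgement can also be influenced by the arm, the loss can differ between arms.

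The reach is wide. The primary outcomes are 7-day point abstinence (PAR), continuous abstinence (CAR), exhaled carbon monoxide (CO), the nicotine withdrawal scale (MNWS) and the stress checklist (SCL). An ordinary illness could plausibly move any of them: a chest infection might bring a week without cigarettes, or raise symptom and stress scores.

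The trial is a pilot, but the Background gives as its aim the calculation of sample size and effect size for later trials. A distorted contrast would carry into those plans.

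**Working it through.** **What the plan's figures allow.** The only relevant figure is the sample size: 3 × 20 = 60, which agrees with the article. It is a convenience sample, with no effect size, significance level or power stated. The concern is therefore established by reading, and the arithmetic only shows how far a few removals could move a contrast.

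**Reading the passages together**

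1. *Criterion.* Expected effect on the outcome measures. No objective definition of the illness or of a significant degree is attached.
2. *Who judges.* The investigators. Participant request is a separate item.
3. *When.* At any time, so also after allocation is disclosed, which the article places on the day treatment starts.
4. *Knowledge of arm.* Arm 3 has no plasters, so Arm 3 can be told from Arms 1 and 2 by sight. For Arm 1 versus Arm 2, the text protects participants and plaster staff and is silent on investigators.

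**Illustration A: one-sided removal**

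Assumptions: 20 per arm, the same true abstinence p in both arms, *k* non-abstainers removed from one arm only, and withdrawn participants left out of the denominator. The removals leave the number of abstainers unchanged, so the mean spurious difference is

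p × 20/(20 − k) − p = p × k/(20 − k).

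| p | k = 2 (p × 2/18) | k = 4 (p × 4/16) |
|---|---|---|
| 20% | 2.2 points | 5.0 points |
| 30% | 3.3 points | 7.5 points |
| 50% | 5.6 points | 12.5 points |

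The plan uses the rank sum test for each pair of arms. For a yes/no outcome with *t* abstainers among *N* = n₁ + n₂ and observed difference *d*:

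- U = n₁n₂(1/2 + d/2)
- Var(U) = (n₁n₂/12) × [(N + 1) − T/(N(N − 1))], with T = t³ − t + (N − t)³ − (N − t)

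I enumerated both binomial counts exactly, at an assumed two-sided level of 0.05. The chance of a significant result favouring the arm with removals is:

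| p | no removals | k = 2 | k = 4 |
|---|---|---|---|
| 20% | 2.5% | 3.7% | 5.2% |
| 30% | 2.7% | 4.3% | 6.3% |
| 50% | 2.1% | 5.9% | 13.4% |

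**Illustration B: worst-case direction**

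Assume 5/20 abstinent in both arms, with two non-abstainers removed from Arm 1 and two abstainers from Arm 3:

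5/18 − 3/18 = 27.8% − 16.7% = 11.1 points.

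One removal per arm in the same directions: 5/19 − 4/19 = 26.3% − 21.1% = 5.3 points.

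**Illustration C: counting withdrawn participants as smokers**

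- Removed non-abstainers: the denominator stays at 20 and their status is unchanged, so the bias in A disappears.
- Removed abstainers: they are now misclassified. Scenario B becomes 5/20 − 3/20 = 25% − 15% = 10 points, hardly less than 11.1.
- CO, MNWS and SCL: the convention supplies no value for these.

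**Illustration D: balanced removal**

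One abstainer and one non-abstainer removed from each arm gives 4/18 v 4/18, no difference. The harm depends on the removals being related to outcome differently by arm.

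**The case against.** The best case for leaving the rule alone has five parts.

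- *The wording is permissive.* Participants may withdraw; nothing forces them out. The sentence that speaks of being withdrawn concerns treatment failure or adverse events, not intercurrent illness. This stands as a limit on how often the rule would be used. It does not change the criterion, which remains the investigators' view of the outcome.
- *Investigator unblinding is not documented.* A reader might infer from the sham section that the principal investigators know who is in which arm. The text does not support that: consultation about whether a point is a true acupoint need not reveal any participant's allocation. This stands. Only Arm 3 is demonstrably open.
- *Adverse effects are handled elsewhere.* A reader might infer that the clause would remove plaster reactions or cessation effects from the safety count. Local plaster effects, severe withdrawal reactions and anxiety are separate grounds, and the article says adverse effects will be recorded. This stands, and I do not claim that the adverse-effect count would fall.
- *The analysis may absorb it.* The article does not say whether withdrawn participants are followed or how they are counted, and an analysis plan may settle that. This stands in part. Counting them as smokers restores a removed non-abstainer, but not a removed abstainer or the missing scale and CO values. A later plan cannot recover assessments that were not made.
- *Few people are affected, in a pilot.* Probably so; the documents give no expected frequency. This bears on the size of the problem, not on whether the rule is sound.

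**Conclusion.** The point holds in a limited form. The protocol states a ground for leaving the study after randomisation that is defined by expected effect on the outcome, rests on investigator judgement, and is not stated to be applied blind to arm. It exposes both comparisons with Arm 3 to differential loss. For Arm 1 versus Arm 2 that exposure is possible but not shown.

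If withdrawn participants leave the denominator and there is no true effect, two one-sided removals shift the abstinence contrast by about 2 to 6 points at 20% to 50% abstinence. The 11-point figure is correct arithmetic on an extreme pattern of four removals sorted by outcome in opposite directions. A reader might take it as the bias to expect, and the documents give no basis for that. Nor do they show that any such removals would be made with intent, or that the judges would know the arm in the true-versus-sham comparison.

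An amendment is worthwhile because the rule is stated, its effect cannot be fully repaired in analysis, and the change is small.

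**What to change.** - Delete expected effect on the outcome measures as a reason for withdrawal from the study.
- Separate stopping the intervention from leaving the study. Whether and when the intervention stops stays with the investigators' clinical judgement and is not addressed here.
- Where consent allows, continue the scheduled assessments after an intercurrent illness and analyse every participant in the randomised arm.
- Record the illness and its date. Confine any exclusion for it to a sensitivity analysis, with cases flagged by someone unaware of the arm.

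The cost is a short amendment and slightly noisier data from the few participants who are ill. The gain has a limit: under the outcome measures section, only successful quitters are assessed at weeks 13 and 26. For non-quitters the change therefore preserves the weekly assessments to week 7 and the expectancy rating at about week 8, and nothing later.

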### Ethics

Consent will be obtained from every participant in a written form. This study protocol has been peer-reviewed and approved by the Queen's University Health Sciences and Affiliated Teaching Hospitals Research Ethics Board. Registration number for ClinicalTrials.gov is.

## Abbreviations

BMI: Body mass index; CAR: Continuous abstinence rate; CO: Carbon monoxide; CSPC: Centre of studies in primary care; MNWS: Minnesota nicotine withdrawal scale; NADA: National acupuncture detoxification association; QUFHT: Queen's university family health team; SCL: Stress Check List; SD: Standard deviation; PAR: Point abstinence rate.
